**Fig 2 pone.0292864.g002:**
[figure not shown]
Blocks (iii)-(iv) graphical representation. (A) target reaching; (B) forearm bisection task. The red circles symbolize the passive retroreflective markers. The subjects’ hand is represented in white and the experimenter’s hand is represented in black.

*(iv) Forearm bisection task (10 min)*. The task will be used to test the representation of the metric properties of the body. In each trial, subjects will be repeatedly asked to point, with the index finger of the non-dominant hand, the midpoint of their dominant forearm (Fig 2B). Subjects will be required to return the non-dominant arm to the starting position at the end of each trial and to wait for a start signal from the experimenter to perform the movement. The task will be repeated 10 times. The midpoint of the subjects’ arm will be calculated as the difference between the y-coordinates of the markers placed on the dominant arm. The distance between the midpoint of the subject’s arm and the selected location of the subject will be calculated as a measure of movement accuracy (see S1 Appendix for details).

*(v.i) Cognitive and behavioral assessment—Body Uneasiness Test (BUT—10 min)*. To test body image self-attitude, we will administer the Italian validated version of BUT [35]. BUT is a 71-item self-report questionnaire that includes a first part (BUT-A) assessing body image concerns, weight phobia, avoidance behaviors, compulsive self-monitoring, detachment, and estrangement feelings toward one’s own body (34 statements), and a second part (BUT-B) which looks at worries related to specific body parts. Each item is rated on a six-point scale ranging from 0 (never) to 5 (always).

*(v.ii) Cognitive and behavioral assessment—Computerized body self-recognition task (15–20 min)*. Selective attention to body parts that do not like (attentional bias) will be assessed using a computerized body self-recognition task (readaptation of the task adopted by [36]). During the task, subjects, seated in front of a monitor, at a distance of about 30 cm, will be presented with three vertically aligned square grayscale images depicting the body parts of other people or their own body parts. The body parts presented could be disease relevant (i.e., shoulders, back) or irrelevant (i.e., leg, arm, hand, foot). Subjects will be instructed to decide as accurately and fast as possible which of the upper or lower images is of the same person as the central target stimulus presented in a red frame. The duration of the trial will not be limited and no pressure will be exerted on the performance of the subjects. Accuracy and reaction times will be collected as outcome variables. See S1 Appendix for more details.

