Body schema is generally assessed using self-reported assessment scales [26]. We propose two ad-hoc tasks to monitor it in a longitudinal study. (i) The *forearm bisection task* is a simple and common test widely used in clinical and research fields to investigate the body schema [27]. It requires the subjects to point to the perceived midpoint of their forearm. Since AIS significantly changes the structure of the adolescent spine, thorax, and trunk, we include an innovative task that involves the movement of the trunk. (ii) The *target reaching* forces the subjects to perform forward trunk movements. It aims to investigate the body schema in adolescent girls with AIS and to determine if alterations in the body schema can modify the planning of movement within the action space immediately surrounding the body, also known as the peripersonal space. The outcomes of the target reaching will be compared with those resulting from the standardized forearm bisection task, to ensure its reliability as a task to evaluate the body schema in adolescents with AIS. During these two tasks, the performance of the subjects will be quantitatively assessed using EEG, marker-based stereophotogrammetry, IMUs, sEMG, and force plates. The EEG signal allows us to quantitatively record the activation of the sensorimotor cortex where the body schema is ‘dynamically’ represented. In fact, the representation of the body schema is plastic and can vary [27]. Marker-based stereophotogrammetry will allow us to accurately estimate the timing of each movement and to relate IMU, sEMG and force plate signals with the EEG.

Body image has been largely neglected in clinical practice and is generally assessed with self-reported questionnaires, which are not capable of detecting the complexity of body image alterations. We propose (i) a self-reported questionnaire and (ii) a computer-based test to investigate body image alterations.

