#### Foreseen data processing

We will investigate both linear (i.e., power spectral density [37], time-varying connectivity [38]) and nonlinear EEG features (i.e., entropy and fractal properties [39, 40] in the scalp and inverse domains (Electrical Source Imaging [41]) from the data recorded at rest and during the execution of target reaching. The laterality index, which describes the contrast in amount of activation (i.e., relative power in the alpha band) between the right and left hemispheres, will be calculated during the target reaching.

In parallel to the quantification of EEG characteristics, the Root Mean Square (RMS) value will be estimated for each sEMG signal, normalized by the MVC, to compare muscular activity within and between groups and investigate possible imbalances in activation patterns between the right and left sides of the body. sEMG signals acquired from the trunk and abdominal muscles during the resting state and the target reaching tasks will allow us to quantify a possible imbalance in the muscle activation pattern between the left and right sides of the body, as reported in previous studies.

Sensors in the trunk and legs will be used to assess the sway and oscillations of subjects at the level of the upper and lower body, respectively, during resting state and the target reaching. Force plates will measure the displacement of the COP, and the motion capture system will allow tracking of arm movement during the target reaching and forearm bisection tasks. In particular, COP data will be used to measure the range of motion in the anterior-posterior (AP) and medial-lateral (ML) directions, the Sway Path length (SP) and the area of the ellipse containing the 95% of the COP trajectory to assess balance during the resting state and target reaching tasks [42, 43]. The data gathered from the waist-mounted IMU [39, 44–46], will be used to evaluate an index of performance quality, complexity and smoothness of motion. To assess possible body schema alterations we will evaluate the task execution accuracy, calculating the Euclidean distance between the actual and the subject selected targets (see S1 Appendix for details).

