Body schema refers to the sensorimotor body representation that entails tracking and updating the position and configuration of both body parts and other objects in space towards which reaching movements can be planned [27]. The functional representation of the action space immediately surrounding the body, also known as the peripersonal space, usually undergoes changes concurrent with body schema alterations. Through the target reaching we will assess if possible body schema alterations in adolescent girls with AIS can alter the planning of the movement within the peripersonal space. The forearm bisection task is a simple and common test widely used in clinical and research fields to investigate the body schema [27]. We will use this task to test whether adolescent girls with AIS have a different representation of the metric properties of their own body compared to CTRL. By replicating the same tasks at time T1 and T2, we will test how the body schema will change as a function of control postural exercises or the effectiveness of brace therapy. The first test of the body schema (T0) is expected to highlight a possible alteration in the perception of the shoulders-waist proportion and in the inclination of the trunk. We expect a decrease in alteration in their body representation due to the treatment. The two tasks are designed to reveal body schema alterations at T0 in the AIS group, which should improve significantly after the 6 month exercise and brace-treatment period (T1).

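### The forearm midpoint is defined as a difference of marker y-coordinates, which is a separation and not a location, so the bisection accuracy score is wrong as written

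*Protocol article*

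**What the plan says.** In the protocol article, under Experimental protocol, block (iv), each girl is asked to "point, with the index finger of the non-dominant hand, the midpoint of their dominant forearm", ten times. The true midpoint "will be calculated as the difference between the y-coordinates of the markers placed on the dominant arm". The outcome follows directly: "The distance between the midpoint of the subject’s arm and the selected location of the subject will be calculated as a measure of movement accuracy". The block refers to S1 Appendix for details.

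Foreseen data processing returns to body-schema accuracy only in general terms, "calculating the Euclidean distance between the actual and the subject selected targets". It gives no other formula for the forearm midpoint.

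The Introduction makes this task the yardstick for the new one: the results of target reaching "will be compared with those resulting from the standardized forearm bisection task, to ensure its reliability". The Discussion says that the bisection task will test whether girls with AIS "have a different representation of the metric properties of their own body compared to CTRL", and it counts on the task to remain informative if follow-up is incomplete.

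**The concern.** The girl points to a place on her arm. The number her pointing is compared with must also be a place, in the same coordinate system. The stated rule supplies a length instead. Subtracting a length from a position gives a number that changes when the origin moves, although the girl has done nothing different, and that changes with marker separation even when she points perfectly.

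Only two tasks measure body schema, and this is the established one against which the new task is checked. If the sentence were followed literally, both the AIS versus control comparison and the check of target reaching would use a score that does not measure bisection error. A reader trying to reproduce the outcome from the article would compute the wrong quantity.

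There is also a smaller point about the form of the score. It is an unsigned distance in raw units, so it cannot show whether girls point too far towards the wrist or towards the elbow, and it is not scaled for limb size in girls aged 11 to 16 who are followed for 12 months.

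**Working it through.** The plan states no figure for this outcome, so there is nothing to reproduce. The check concerns the formula.

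**Inputs.** From block (iv): midpoint rule = difference of marker y-coordinates; score = distance from that midpoint to the pointed location. Not given in the shown text: the number and position of the markers, the direction of the axis, the origin, and the forearm length. For illustration I assume two end markers at y1 (elbow) and y2 (wrist), a forearm lying along y, subtraction of the smaller coordinate from the larger, and a separation L = y2 − y1 of 220 mm (range 200 to 240 mm).

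**Formulas.**
- Midpoint: M = (y1 + y2)/2.
- Rule as written: D = y2 − y1.
- A girl who points exactly to the midpoint has p = M, and the rule scores her |M − D| = |3·y1 − y2|/2. With y2 = y1 + L this is |y1 − L/2|.

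This is zero only when y2 = 3·y1, a coincidence of where the origin lies. Otherwise it depends on y1 (the origin) and L (the separation), and on nothing the girl did.

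**Perfect pointing under assumed origins (mm).**

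| y1 | y2 | D (as written) | M (true) | Score as written | Score with M |
|---|---|---|---|---|---|
| 0 | 200 | 200 | 100 | 100 | 0 |
| 0 | 220 | 220 | 110 | 110 | 0 |
| 0 | 240 | 240 | 120 | 120 | 0 |
| −110 | 110 | 220 | 0 | 220 | 0 |
| 100 | 320 | 220 | 210 | 10 | 0 |
| 110 | 330 | 220 | 220 | 0 | 0 |
| 300 | 520 | 220 | 410 | 190 | 0 |

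The table shows dependence on the origin. It is not a range of likely error, because the origin is not stated and other choices give other values.

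**Origin at the elbow marker.** Here D = L = y2, so the rule places the target at the wrist marker. The score for perfect pointing is L/2 and is determined entirely by L. An error e towards the wrist (smaller than L/2) gives L/2 − e. With L = 220, an error of +20 mm scores 110 − 20 = 90, and one of −20 mm scores 110 + 20 = 130. The correct formula scores 20 for both. Under the written rule, pointing too far towards the wrist would therefore look more accurate than perfect pointing.

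**Secondary point, with the correct midpoint.** Errors of +20 mm and −20 mm both score 20 mm, so direction is lost. A constant proportional error of, say, 10% of length is 0.10 × 200 = 20 mm on a 200 mm forearm and 0.10 × 240 = 24 mm on a 240 mm forearm, so a raw distance moves with limb size.

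**The case against.** The strongest reply is that this is a slip of wording. The intent is clear from the neighbouring sentences: the girl points to the midpoint and is scored on her distance from it. A word such as mean, or half the difference measured from one marker, may have been meant. Details are referred to S1 Appendix, which is not shown, and neither is the figure with the markers. The code may well be right. All of this stands, and it limits the finding to the definition as written. It does not remove the finding: the article states a specific wrong rule, which is different from leaving a detail to another document.

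Several stronger readings are tempting, and the documents do not support them:

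- *Group and time differences will reflect position and growth.* This assumes that the sentence is coded literally in an uncontrolled laboratory frame. Nothing shown establishes that, and the score can be recomputed from marker coordinates without loss of data.
- *The stated quantity is the forearm length.* That requires markers at both ends and a forearm along y. The text says only that markers are on the dominant arm. In any case the quantity is a separation and not a midpoint.
- *Seating alone produces an artefact of a given size.* No origin is stated, and the article describes girls as seated only for the computer task.
- *An unsigned score is an error.* The outcome "will be calculated as a measure of movement accuracy", for which an unsigned distance is legitimate, and no direction is hypothesised. Lack of scaling is partly covered by matched controls remeasured at 12 months, although controls have no 6-month visit.

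The sample size is unaffected, because it rests on the EEG laterality index.

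**Conclusion.** The point holds as a wrong definition. As written, the midpoint is a separation along y, so the distance built on it is not a bisection error and depends on the origin and the marker separation. With the origin at one end marker, perfect pointing scores half the separation: 100 to 120 mm for assumed separations of 200 to 240 mm, against 0 under the correct formula. These sizes rest on assumed marker positions and a forearm along y. That a difference is not a midpoint rests on neither assumption.

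It should be corrected because the task is the reference for target reaching and one of only two body-schema tasks. Whether the outcome itself will be miscalculated cannot be judged without S1 Appendix and the code. Signed and length-scaled reporting is an improvement and not the correction of an error.

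**What to change.** Replace the sentence in block (iv) so that the midpoint is the mean of the coordinates of the two forearm end markers, (y1 + y2)/2. Name the two markers and the axis, and state that the pointed location is measured in the same frame. Check that S1 Appendix and the processing code use this formula, and recompute from stored coordinates any scores already produced under another rule.

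As an optional addition, report the signed error as a percentage of forearm length, 100 × (p − M)/L, positive towards the wrist and averaged over the ten trials, next to the unsigned distance.

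The cost is about one line of text and one of code, plus a check of the appendix. If the named end markers are those already placed on the arm, no new measurement is needed.

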#### Foreseen data processing

We will investigate both linear (i.e., power spectral density [37], time-varying connectivity [38]) and nonlinear EEG features (i.e., entropy and fractal properties [39, 40] in the scalp and inverse domains (Electrical Source Imaging [41]) from the data recorded at rest and during the execution of target reaching. The laterality index, which describes the contrast in amount of activation (i.e., relative power in the alpha band) between the right and left hemispheres, will be calculated during the target reaching.

In parallel to the quantification of EEG characteristics, the Root Mean Square (RMS) value will be estimated for each sEMG signal, normalized by the MVC, to compare muscular activity within and between groups and investigate possible imbalances in activation patterns between the right and left sides of the body. sEMG signals acquired from the trunk and abdominal muscles during the resting state and the target reaching tasks will allow us to quantify a possible imbalance in the muscle activation pattern between the left and right sides of the body, as reported in previous studies.

Sensors in the trunk and legs will be used to assess the sway and oscillations of subjects at the level of the upper and lower body, respectively, during resting state and the target reaching. Force plates will measure the displacement of the COP, and the motion capture system will allow tracking of arm movement during the target reaching and forearm bisection tasks. In particular, COP data will be used to measure the range of motion in the anterior-posterior (AP) and medial-lateral (ML) directions, the Sway Path length (SP) and the area of the ellipse containing the 95% of the COP trajectory to assess balance during the resting state and target reaching tasks [42, 43]. The data gathered from the waist-mounted IMU [39, 44–46], will be used to evaluate an index of performance quality, complexity and smoothness of motion. To assess possible body schema alterations we will evaluate the task execution accuracy, calculating the Euclidean distance between the actual and the subject selected targets (see S1 Appendix for details).

To reveal possible alterations in body image representation in adolescent girls with AIS, BUT sub-scores will be calculated (scoring instructions are reported in S1 Appendix). Response accuracy (i.e., percentage number of correct responses over the total number of trials) and reaction times (RTs), collected as outcome variables during the Computerized body self-recognition task, trials will be clustered according to the target stimulus and subsequently analysed. The correlations between the BUT questionnaire subscores and RTs and accuracy will be assessed using the Pearson’s correlation coefficient (r).

The results of AIS-adolescent girls and controls of the same age and sex will be compared by statistical analyses. Shapiro-Wilk normality test will be applied on all the data collected to check the normal distribution. A two-tailed paired sample t-test or a two-sided Wilcoxon rank sum test (*p* < 0.05) will identify differences between the two groups (AIS vs. CTRL) and between the three time points evaluation (T1, T0 and T2) after having run a global test (either repeated measure ANOVA, or Friedman test depending on data normality).

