**Methods:**

Adolescent girls with a confirmed diagnosis of mild (Cobb angle: 10°-20°) or moderate (21°-35°) scoliosis as well as age and sex-matched controls will be recruited. Participants will be asked to perform a 6-min upright standing and two tasks—named target reaching and forearm bisection task. Eventually, subjects will fill in a self-report questionnaire and a computer-based test to assess body image. This evaluation will be repeated after 6 and 12 months of treatment (i.e., partial or full-time brace and physiotherapy corrective postural exercises).

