## Materials and methods

### Experimental design

Adolescent girls with a confirmed diagnosis of mild (Cobb angle ranging from 10° to 20°, no spine surgery) and moderate (Cobb angle ranging from 21° to 35°, no spine surgery) scoliosis (AIS) will be enrolled at the Adolescence Spine Diseases Diagnostic and Therapeutic Center of the Padova University Hospital. Subjects matched in sex and age without AIS—controls (CTRL)—will be recruited through flyers posted in middle and high schools in Padova.

Adolescent girls with AIS and controls will undergo a three-phase experimental protocol (T0, T1, T2).

This longitudinal study aims to follow and quantify alteration in body representation in parallel to the progression of scoliosis from the time of the first diagnosis by the physiatrist (T0) and up to one year after diagnosis (T1, T2). At T0, subjects (AIS and CTRL) will undergo two tasks aimed at investigating possible alterations in *body schema* representation. During the experiment, we will use EEG to record changes in brain oscillations; sEMG to assess possible imbalances in muscle activation, IMUs, motion capture, and force platforms to monitor the performance and movement characteristics during the balance and motor tasks. A self-reported questionnaire and a computer-based test will be administered to all subjects to investigate *body image* alterations in AIS.

After this evaluation (T0), if the adolescent shows low-grade scoliosis, an expert physiotherapist gives her corrective postural exercises to perform daily (30 min / day) until growth is complete. Participants’ performance in scoliosis-specific exercise will be monitored by the physiotherapist at least once a week. The set of exercises is believed to improve postural awareness, proprioception, and ability to dissociate the movements of the lumbar spine from the thoracic one in the different planes of space. Treatment will be planned in the individual patient, based on the dysfunction detected in the clinical assessment. When scoliosis exceeds the 20°Cobb and there is evidence of progression risk, a rigid partial (18 hours/day) or full-time brace (23 hours/day) is also prescribed.

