#### Clinical assessment

Before undergoing the experimental protocol, the following data will be recorded for each subject: age, weight, height, BMI, sexual maturity, evaluated according to information related to menarche, and physical activity. Handedness will be evaluated using the Oldfield Questionnaire [28].

During their first medical examination, adolescents with AIS will undergo a physical assessment performed by a physiatrist to (i) detect the presence of possible body asymmetries and (ii) measure the paravertebral humps in the forward bent position with the Bunnell scoliometer and the Ferraro humpmeter [29, 30]. All subjects will be evaluated by the same physiatrist to ensure data repeatability and minimize intersubject measurement error. A standing full-spine posterior-anterior x-ray will be performed. The curve entity will be quantified using the Cobb angle method [31], while the Perdriolle method will be applied to estimate the rotation of the apical vertebrae [5]. Based on the radiological image, the physiatrist will also collect other relevant clinical measures, i.e., the initial correction rate (ICR), the side and anatomical site of the convexity of the scoliosis, trunk asymmetries, shoulders, and hips inclination. Radiological examination will be repeated only at T2 to avoid excessive radiation exposure in adolescent girls, allowing clinicians to quantify possible variations in the values of the parameters. The progression of AIS will be defined as a worsening of more than 5°Cobb in the magnitude of the curve during the duration of the study (approximately one year). Therapy specifics (e.g., brace type, prescription, compliance, duration of exercise) will be reported both for subjects who will be treated with a partial or full-time brace and for those who will only be assisted with corrective postural exercises (for more details, see Fig 1).

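### The AIS versus control comparison has no age term, and whether the age matching is used at all depends on a normality test

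*Protocol article*

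**What the plan says.** Experimental design states: "Subjects matched in sex and age without AIS—controls (CTRL)—will be recruited through flyers posted in middle and high schools in Padova". The abstract repeats the age and sex matching. Selection criteria give 11–16 years for both groups. Clinical assessment lists what is recorded for each subject: "age, weight, height, BMI, sexual maturity, evaluated according to information related to menarche, and physical activity".

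Foreseen data processing introduces the group comparison with "The results of AIS-adolescent girls and controls of the same age and sex will be compared by statistical analyses" and then fixes the tests. After a Shapiro-Wilk check and a global test (repeated measures ANOVA or Friedman), "A two-tailed paired sample t-test or a two-sided Wilcoxon rank sum test" at p < 0.05 "will identify differences between the two groups (AIS vs. CTRL) and between the three time points evaluation (T1, T0 and T2". One sentence therefore covers both the group contrast and the comparisons over time. No test in that section includes age.

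Procedure expects 15 girls with AIS and 15 controls to be analysed, at 5% alpha and 80% power. The effect size is taken from the sponsor's previous study and is not printed.

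**The concern.** Age is the one matching factor that varies, because every participant is female. When a design matches on a variable, the analysis should normally use it, for two reasons.

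- **Close matching.** The two groups become positively correlated through age. A test that treats them as independent then has too large a standard error.
- **Loose matching.** The age difference is carried into the estimated AIS effect. Controls are volunteers who answer school flyers and the AIS girls come from one hospital centre, so with about 15 per group a gap in mean age is possible.

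The plan's two tests deal with this differently. A paired t-test uses the matching if the pairs are age-matched AIS–control pairs. The rank sum test treats the groups as independent. The choice rests on a Shapiro-Wilk result, so matching could count for one outcome and not for the next. The untreated comparison at T0 is central to the article's hypotheses.

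**Working it through.** **Inputs from the article:** 15 per group; two-sided 5%; 80% power; ages 11–16. **Assumptions:** ages uniform over that range, so SD = 5/√12 = 1.44 years; a linear age effect with within-group correlation rho, which the article does not give; no within-pair correlation beyond age.

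**1. The plan's own figure.** The effect size is not printed, so 15 per group can be neither confirmed nor refuted. Solving backwards with the noncentral t (28 df), 15 per group has 80% power at d = 1.06. For 15 pairs analysed as pairs, the corresponding value is dz = 0.78.

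**2. Power with age as a covariate, ages balanced.** Residual SD shrinks by √(1 − rho²), so the noncentrality is d/√(1 − rho²) × √(15/2) on 27 df. At rho 0.5 this is 1.06/0.866 × 2.739 = 3.35.

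| rho | 0 | 0.1 | 0.2 | 0.3 | 0.4 | 0.5 |
|---|---|---|---|---|---|---|
| Power | 79.9% | 80.3% | 81.5% | 83.5% | 86.3% | 89.8% |

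**3. Close matching** (pairs within half a year, simulated, 200,000 runs per setting, d = 1.06 for power):

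| | Unpaired t | Rank sum | Paired t | Age-adjusted |
|---|---|---|---|---|
| Power, rho 0 | 80.1% | 76.6% | 77.1% | 80.0% |
| Power, rho 0.3 | 81.0% | 77.3% | 80.8% | 83.5% |
| Power, rho 0.5 | 83.0% | 79.0% | 87.4% | 89.8% |
| Type I error, rho 0.5 | 2.5% | 2.3% | 5.0% | 5.0% |

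At rho 0.5 the paired t-test loses 89.8 − 87.4 = 2.4 points. The rank sum test loses 89.8 − 79.0 = 10.8 points. Part of that is the cost of ranking: at rho 0 it already loses 80.0 − 76.6 = 3.4.

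**4. Residual age gap.** The bias in the unadjusted difference is rho × gap / 1.44 SD. A half-year gap gives 0.10 SD at rho 0.3 and 0.17 at rho 0.5. A 1-year gap gives 0.21 and 0.35 SD. Pairing does not remove it. Simulated type I error with a 1-year mean gap (pairs otherwise within half a year of that offset):

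| | Unpaired t | Rank sum | Paired t | Age-adjusted |
|---|---|---|---|---|
| rho 0.3 | 7.5% | 6.8% | 8.6% | 4.9% |
| rho 0.5 | 11.7% | 10.4% | 17.5% | 5.1% |

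The paired test does worst here because its smaller standard error is centred on a biased difference.

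**5. Cost of adjusting when age does not matter (rho 0).** In the same simulation, power falls from 80.0% (unpaired t) to 78.5% with a half-year gap and to 74.7% with a 1-year gap. With the two groups' ages drawn independently, the loss is about 2 and 6 points.

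**The case against.** The strongest objection is that the plan names a paired t-test. In a study with age-matched controls, that is a recognised way to use the matching. A reader might infer that the group comparison ignores age altogether, and the text does not support that. On age-matched pairs the paired test keeps its 5% level and comes within 2 to 3 points of the adjusted model. The 2.5% type I error and 83% power at rho 0.5 belong to an unpaired t-test, which the plan does not name. Only the rank sum branch behaves in that way.

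Three further points count against a strong reading:

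- The article gives no age–outcome correlation, and nothing in it says that the EEG laterality index, on which the study is sized, varies with age between 11 and 16. At rho 0.2 or below the gain is under 2 points.
- Loss of power under close matching and bias under loose matching are alternatives, so they cannot be added together.
- A condensed article may leave a matching tolerance to a fuller document. Its absence here is not itself a fault, and the 1-year gap is a scenario, not a prediction.

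Management also says that demographic data will enter the analysis. That sentence sits among confidentiality provisions and names no model or covariate, so it does not change the stated tests.

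What stands is that the two stated branches treat the matching differently, and neither removes a residual age difference.

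**Conclusion.** The point holds in a limited form. The fault lies in tests the article does state: two alternatives for one contrast, one able to use the age matching and one not, chosen by a normality test, with no age term in either. The paired branch works as intended only if AIS–control pairs exist. The wording could equally mean pairing over time points alone.

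The size is conditional on rho. The power at stake is negligible up to rho 0.2. At rho 0.5 with close matching it is 2 to 3 points for the paired t-test and about 11 for the rank sum test. If mean ages differ by a year and rho is 0.3 to 0.5, false-positive rates rise to about 7–17%, depending on the test. These figures assume uniform ages, a linear age effect and 15 per group. This is a worthwhile correction to the analysis wording. It does not show that the planned comparison is invalid or that the sample size is wrong.

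**What to change.** In Foreseen data processing, separate the AIS versus control contrast from the time-point comparisons. For the group contrast, state one analysis for both normality branches: a linear model of the outcome on group and age at assessment (continuous), reporting the adjusted difference with its 95% confidence interval. Where residuals are clearly non-normal, use a rank-based version of the same model or a permutation test of the group term. Keep the tests now named as a sensitivity analysis, and say whether controls are individually paired, since the paired t-test needs that.

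No new data are required, because age is already recorded. The cost is one residual degree of freedom, which is negligible if ages are balanced. If age proves unrelated to the outcome and the groups differ by 0.5 to 1 year, it is about 2 to 6 points of power. The model should therefore be fixed before the T0 data are seen, and not chosen after looking at the age balance.
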